#### Secondary outcomes

The secondary outcomes investigated in this trial include:Differences in ALT, AST, γGT, and AP levels after *versus* before;Difference in ferritin levels after *versus* before;Difference in fasting glucose, insulin, HbA1C, and HOMA-IR levels after *versus* before; andDifference in BMI and WC after *versus* before.

### Participant timeline {13}

Table 1 shows the stages of the study and which assessments will be performed throughout the study period.

**Table 1 Tab1:** Schedule of enrolment, interventions, and assessments

Schedule of activities									
	Enrolment	Allocation	Post-allocation					Close-out	
Time Point	Week 1	Week 2	Week 3–5	Week 6	Week 7–10	Week 11	Week 12–15	Week 16	Week 17
**Enrolment**									
Screening	•								
Eligibility screen	•								
Informed consent	•								
Computed tomography (CT) and collection of laboratory tests	•								
Baseline consultation (allocation)		•							
**Interventions**									
Intervention start		•							
Telephone follow-up			•		•		•		
Return consultation 1				•					
Return consultation 2						•			
Return consultation 3								•	
**Assessments**									
Computed tomography (CT) and laboratory tests								•	
Final consultation									•

### Sample Size {14}

The sample size was determined through an accuracy analysis of the primary outcome. A significance level of 0.05 and a power of 80% were adopted, which resulted in a minimum sample size of approximately 132 participants.

### Recruitment {15}

Patient recruitment started in February 2019 and ended in May 2022. All participants have been diagnosed with NAFLD prior to participation in this trial. All participants were recruited directly from the NHOC, or they have been referred to the NHOC by local health centers located in the neighborhoods of the city of Salvador. The NHOC provides specialist care for patients with liver diseases, including NAFLD. However, only patients diagnosed with NAFLD have been approached to discuss their participation in the trial.

All patients received in May 2022 or onwards a phone call with an invitation for a face-to-face consultation, in which their individual results will be discussed with a clinician researcher. Any current or new need for medical care will be discussed at that consultation, and a new referral will be made if necessary.

The burden of this randomized controlled trial was not assessed by the patients themselves or their families. Prior to signing the consent forms, all patients were reassured that their participation in this trial was entirely voluntary. All patients were also reassured that they could withdraw at any time without giving a reason and reassured that withdrawing would not result in any penalty to them and would not interfere with any current or future medical or healthcare provision to them.

## Intervention assignment: allocation

### Sequence generation {16a}

Patients who agreed to take part in the study and met all the study criteria were assigned to I or C groups by computer-generated randomization in blocks with the aid of a spreadsheet to ensure a random but uniform variation in sizes of each I and C blocks. Randomization and record keeping of all participants were carried out by a statistician researcher external to the research group. The statistician is not involved in patient clinical assessment.

### Concealment mechanism {16}

The allocation sequence was concealed from the researchers assessing participants and their clinical outcomes. The allocation sheet hardcopies are kept in envelopes in a locked drawer of a secure filing cabinet located at the NHOC administrative office.

### Implementation {16c}

All patients who give consent for participation and who fulfill the inclusion criteria are randomly assigned to I or C. The Principal Investigator (PI) will open the envelopes containing the allocation sequence only after the last participant included completes the trial.

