### Data management {19}

The data were collected in paper form and stored in binders, which are kept in a locked drawer of a secure filing cabinet located at the NHOC administrative office. Only the PI has access to the documents.

After data collection, all forms will be checked by two members for data quality and missing information. The data will be entered manually into an electronic spreadsheet and subsequently checked by two researchers, one at a time.

The database and electronic analyses will be stored on a secure computer server with personal login access authorized by the PI. After completion of the study, all data and study documents will be archived and stored by the PI. The data is not public and remains in the possession of the PI. Individual unidentifiable data can be made available upon reasonable request.

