## Statistical methods

### Statistical methods for primary and secondary outcomes {20a}

Statistical analyses will firstly be performed using descriptive analysis to characterize the distribution of the events studied. Categorical variables will be investigated using simple absolute frequencies. Continuous variables will be investigated by measures of central tendency and dispersion. Parametric or non-parametric tests will be used considering the distribution nature of the variables studied. A significance level of 5% will be adopted for all statistical tests. Tests to verify variable behavior and comparisons of proportions analyses, such as the application of the chi-square test or Fisher’s exact test, will be discussed later with a qualified statistician. Tests for comparison of means between groups, analysis of correlations between continuous variables and logistic regression analysis, will also be discussed with the statistician. Data will be tabulated and analyzed using the R Project for Statistical Computing software (R-3.2.4 for Windows).

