## Oversight and monitoring

### Composition of the coordinating center and trial steering committee {5d}

The PI as a blind evaluator and a coordinator assistant will coordinate all phases of the study, the randomization, and record-keeping of I and C participants. Patient and Public Involvement Groups (PPIG) were not involved in the design, recruitment, or execution of this trial, nor will they be involved in the reporting and dissemination of this research trial, with the exception of dissemination through their own social media channels if they wish.

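### Allocation may be opened once the last participant completes, with no requirement that data checking, analysis-set decisions and choice of tests come first; the PI's role in randomisation is also stated inconsistently

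*Protocol article*

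**What the plan says.** **Opening of the allocation.** Under Implementation {16c}, the PI will "open the envelopes containing the allocation sequence only after the last participant included completes the trial". This is the only timing rule for release of the allocation.

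**Work on the data.** Data management {19} states: "After data collection, all forms will be checked by two members for data quality and missing information". The next step is: "The data will be entered manually into an electronic spreadsheet and subsequently checked by two researchers, one at a time". The paper forms are in binders, "kept in a locked drawer of a secure filing cabinet located at the NHOC administrative office. Only the PI has access to the documents". Access to the electronic database is authorised by the PI.

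**Choice of tests.** Statistical methods {20a} says of the tests for proportions that they "will be discussed later with a qualified statistician". Comparisons of means, correlations and logistic regression are likewise left to discussion with the statistician.

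**Analysis set.** Section {20c} restricts the analysis to participants who completed the trial and treats drop-outs as protocol deviations to be left out. It does not say who makes the classification, or whether that person is blind.

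**Who handles allocation.** Sequence generation {16a}: "Randomization and record keeping of all participants were carried out by a statistician researcher external to the research group". Section {17b} limits access to group allocation to the dispensing pharmacist and the statistician. Section {5d} says: "The PI as a blind evaluator and a coordinator assistant will coordinate all phases of the study, the randomization, and record-keeping", and goes on to specify that the records are those of the I and C participants.

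**Where the allocation is kept.** Concealment mechanism {16}: "The allocation sheet hardcopies are kept in envelopes in a locked drawer of a secure filing cabinet located at the NHOC administrative office". No key holder is named.

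**The concern.** The usual safeguard is that nobody who can influence the data or the analysis learns the arms until the data are locked and the analysis is fixed. Here the trigger is an event in participant follow-up, and several discretionary steps can still lie ahead when it occurs: resolving queries on paper forms, deciding who counts as a completer, and choosing the tests. The person who opens the envelopes also controls access to the forms and to the database.

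If these steps are taken with the arms known, each can move the result, and a reader cannot tell afterwards whether it did. The role statements add to the difficulty. A person described as a blind evaluator should not also be described as coordinating the randomisation and the records of who is in which group.

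**Working it through.** The point is procedural, so the check is mainly a comparison of sections.

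**1. Order of events**

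| Step | Time stated | Must it precede opening? |
|---|---|---|
| Outcome assessment | During follow-up, by blinded evaluators ({17a}) | In effect yes |
| Form checking ({19}) | After data collection | Not stated |
| Manual entry and its check ({19}) | Follows form checking | Not stated |
| Classification as completer or deviation ({20c}) | No time given | Not stated |
| Choice of tests ({20a}) | Later | Not stated |
| Opening by the PI ({16c}) | Not before the last participant completes | – |

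Four steps have no stated order relative to opening. Following {16c} to the letter, the PI could open the envelopes on the day the last participant finishes, with all four still to do. The text does not say that this is the intention.

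**2. Could the trigger be met with these steps undone?** Recruitment ended in May 2022 (Recruitment {15}, Trial status) and Table 1 ends at week 17. Taking 31 May 2022 as the latest start, 17 × 7 = 119 days leads to 27 September 2022. The article appeared on 10 March 2023 and still puts data entry, choice of tests and opening in the future tense. Its submission date is not given, so this shows only that such a window is possible, not that early opening occurred.

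**3. Roles**

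| Section | Randomisation and records | Access to allocation |
|---|---|---|
| {16a} | External statistician | – |
| {17b} | – | Pharmacist and statistician only |
| {5d} | Coordinated by the PI (blind evaluator) and a coordinator assistant | – |
| {16c} | – | PI, after the last completion |

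Sections {16a} and {5d} assign the same work to different people. If the PI's coordination involves sight of the I and C records, {5d} also conflicts with {17b} and with the PI's description as blind.

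**4. Custody.** The envelope drawer in {16} and the data drawer in {19} are described in the same words. Sole PI access is stated for the data documents. For the envelopes no holder is stated.

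**5. Reversibility.** Section {26b} says that data of withdrawn or lost participants will be deleted. A contested exclusion could then not be re-examined.

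**6. Size, as illustration only.** No figure in the document measures this problem. What can be illustrated is the effect of an open choice of analysis. Inputs: 132 participants ({14}), taken as 132 / 2 = 66 per arm (1:1 is an assumption); normal data; no true effect; an assumed correlation between baseline and final values; assumed cut-offs for resolution and improvement. Five analyses of the primary measurement are run and the smallest p-value is kept: t-test of change, Mann-Whitney test of change, t-test of final value, chi-square test of resolution, chi-square test of improvement.

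- One simulation: 13.3%, 15.3% and 14.8% of null trials fall below 0.05, at correlations 0.6, 0.7 and 0.8.
- A second, independently written (10,000 trials per setting): 14.8% and 16.6%, at correlations 0.5 and 0.7. Each single test stayed between 4.5% and 5.4%.

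For comparison, five independent tests would give 1 − 0.95^5 = 22.6%. The simulated values are lower because the five analyses are correlated.

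**The case against.** The strongest reply has five parts.

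- **Earliest time only.** Section {16c} says when the envelopes may not be opened. A reader might infer that they are to be opened before entry, exclusions and test choice. The document does not say so.
- **Custody.** A reader might infer from the matching descriptions that the PI holds the envelope drawer. The access statement in {19} concerns the data forms, and like wording does not show that it is the same drawer or key.
- **Blinded assessment and exclusions.** Clinical assessments are stated to be blinded, and opening follows the last completion, so the trigger does not undermine outcome assessment. Many exclusions (missed phases, new diagnoses, moving away) arise during follow-up, before opening is allowed.
- **Other safeguards.** Forms and entry are checked by two people, section {23} has an external researcher verify the data, and blood results come from the laboratory's own system.
- **Scope.** Database lock and test specification are often left to a fuller protocol or an analysis plan, neither of which is shown. Coordination in {5d} may mean only oversight.

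The first three parts stand, and they limit the concern to decisions made after data collection. The fourth stands in part: these checks reduce error, but none is linked to unblinding and none covers the analysis set or the tests. The fifth does not remove the point. The article itself fixes a trigger that allows the problem and itself defers the tests, and the conflict between {5d} and {16a} is internal to it.

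**Conclusion.** The concern holds in limited form. The plan permits data checking and entry, analysis-set decisions and choice of tests to be settled with the arms known, because opening is tied only to the last participant's completion. It does not prescribe that order, and nothing in the document shows that it happened. Separately, the account of who handles randomisation and group records is contradictory, and custody of the envelopes is not separated from the PI.

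The document does not support concluding that the PI knew the allocation during the trial, or that the blinded outcome assessments are unsound.

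The size of any bias cannot be derived from the document. The 13–17% type I error is a worst case for selecting among five analyses, under assumed correlations, cut-offs and equal arms. It is not an effect of unblinding time as such. The point still deserves action, because once the arms are known the lapse can be disclosed but not repaired.

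**What to change.** 1. In {16c}, replace the trigger: allocation is released only after checked data entry, analysis-set decisions made and recorded blind, database lock, and a dated and signed analysis plan.
2. Reconcile {5d} with {16a} and {17b}, so that one account states who generates the sequence, who keeps the group records and who has access to them.
3. In {16}, name a custodian of the envelopes other than the PI.
4. If the envelopes are already open, report the date of opening relative to data lock and to fixing of the analysis, and do not describe data cleaning or analysis decisions made after that date as blinded. Recruitment ended in May 2022, so this may be the only remedy left for the first item.

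The cost is a few sentences of text, moving the envelopes, a dated sign-off and a short delay before unblinding.

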## Assignment of interventions: blinding

### Who will be blinded {17a}

All clinical assessments were conducted by evaluators blinded to treatment allocation. Participants were blinded to the study hypothesis and their allocation group, but were advised of the overall aspects involved in the treatment of both groups. I and C capsules were dispensed by a registered pharmacist at the clinical research pharmacy of the Teaching Hospital where the trial took place. The pharmacist was responsible for receiving and storing all batches of I and C capsules manufactured by Singular Pharma, as well as identifying the correct capsule to be dispensed according to the specific numbering of each participant.

### Procedure for unblinding if needed {17b}

The trial design is open-label with outcome assessors being blinded. Only the pharmacist in charge of dispensing the trial capsules and the statistician have access to group allocation; neither, however, are involved in clinical assessment or data collection.

### Data collection and management {18a}

The research team involved in this trial underwent training prior to commencement of the study regarding the protocol to be followed, to avoid biases and errors in data collection. The clinical dietitians ([name], [name], [name], [name]) in charge of seeing patients at the NHOC performed a triage of eligible patients, and the more experienced dietitian running the clinic ([name]) was responsible for double-checking that all the inclusion and non-inclusion criteria had been fully met for each patient. [name] was also responsible for explaining the study in further detail and taking verbal and written consent. The clinical trial is structured as presented in Table 1 and detailed below.

#### Screening

Patients who meet the eligibility criteria are referred to the screening consultation to receive information about the clinical trial and are given the opportunity to ask questions to the research team. Consenting participants are invited to sign the free and informed consent form. All participants are informed that they can withdraw at any time without giving reasons and that they will not be penalized for withdrawing. After signing the consent form, all participants answer questions on a standardized form filled in by the researcher. Information on sociodemographics, clinical history and clinical presentation, lifestyle data, diet intake, and feeding patterns are collected. The first anthropometric assessment is completed at that point.

At the end of the screening consultation, participants receive general nutritional guidelines and a study identification card with the contact details of the researchers. Participants are encouraged to make contact should they have any late questions about the trial. Following the first appointment, participants are referred to an upper abdomen CT scan before the intervention begins.

##### CT scans

Participants undergo a scheduled upper abdomen CT scan at the Radiology Unit of the [name] University Hospital Complex. NAFLD is confirmed by a radiologist consultant. Patients who do not present NAFLD at the CT scan, even if they have historical imaging tests diagnosing the disease at an earlier period, are excluded from this trial and referred to a consultation with a registered nutritionist to receive specific guidelines on how to prevent NAFLD recurrence,

##### Blood tests

After the CT scan, participants are taken a 12-h fasting venous blood sample. They are given a breakfast meal after the blood sample collection and are given the details of their next consultation.

#### Allocation consultation

At this appointment, participants receive their CT scan and blood test results and are submitted to a second anthropometric assessment. At this consultation, a new form with nutritional and dietary data is completed by the researcher, and patients are given additional nutritional guidelines to complement the advice offered in the screening appointment. Subsequently, participants are sent to the clinical research pharmacy of the Hospital Complex for capsule collection according to their randomization.

#### Monthly follow-up visits (return visits 1, 2, and 3)

All participants were followed up through face-to-face individual consultations in 4-week intervals during the 12-week supplementation period. The Return Visits were scheduled as detailed in Table 1. At these appointments, patients were asked about adherence to the study. They were asked to bring along to each consultation the flasks they receive containing the capsules from the previous 4-week period, so that the research team can more accurately estimate adherence to the protocol.

At each monthly follow-up visit participants had a nutritional and dietary assessment undertaken by a registered nutritionist member of the research team. The researcher completed a form with dietary intake and dietary habits over the last 4-week period and evaluated adherence to nutritional guidelines, ingestion of capsules as prescribed, tolerance, and the occurrence of any adverse effects.

#### Telephone follow-up

except for the weeks when participants had their scheduled Return Visits, all participants were contacted weekly by telephone to monitor adherence to the protocol, clarify any questions, and report any occurrence or adverse reactions.

At Return Visit 3, which took place at the end of the 12^th^ week of intervention, patients were referred to a second CT scan and blood tests following the same protocols as the baseline tests. A final consultation was scheduled for the test results to be delivered (Table 1).

In the final consultation, participants who no longer showed fatty infiltration received guidance on how to prevent the recurrence of NAFLD. Participants who showed evidence of NAFLD, regardless of the degree of steatosis, were referred to the outpatient follow-up clinic for continuation of their care provision with a hepatologist consultant and a registered nutritionist (Fig. 1).

### Plans to promote participant retention and complete follow-up {18b}

Participants received information about the study design and the importance of completing the final follow-up. The research team contacted the participants via telephone calls, and in case of not reaching, a voice message or text message 24 h before the scheduled appointments and blood tests, aiming to minimize non-attendance.

### Data management {19}

The data were collected in paper form and stored in binders, which are kept in a locked drawer of a secure filing cabinet located at the NHOC administrative office. Only the PI has access to the documents.

After data collection, all forms will be checked by two members for data quality and missing information. The data will be entered manually into an electronic spreadsheet and subsequently checked by two researchers, one at a time.

The database and electronic analyses will be stored on a secure computer server with personal login access authorized by the PI. After completion of the study, all data and study documents will be archived and stored by the PI. The data is not public and remains in the possession of the PI. Individual unidentifiable data can be made available upon reasonable request.

### Confidentiality {27}

The data will be treated anonymously and confidentially and at no time will the personal details of the participants be disclosed at any stage of the study.

### Plans for collection, laboratory evaluation, and storage of biological specimens for genetic or molecular analysis in this trial/future use {33}

Blood tests were performed following standardized laboratory protocols for medical diagnosis in humans. Blood samples were not stored for genetic or molecular analysis in the current study or any other future use. Blood samples were discarded following standardized hospital protocol. Blood test results were collected from the clinical analysis laboratory of the Institute of Pharmacy of the Federal University of Bahia via a secure hospital intranet.

